#### Sample size calculation

The required patient number was assessed using the software R with a simulation of 9999 iterations. 251 patients per trial arm are required for a power of 97.5% with reference to cosmetic result and 82.5% with reference to local control, considering a drop-out rate of 10%. The assumed drop-out rate includes patients, who withdraw their consent to participate after randomization, as well as patients who are not treated according to the protocol, do not meet inclusion criteria or meet exclusion criteria, whose data files are incomplete or whose status is not properly assessed by follow-up examinations.

#### Analysis methods

Differences in the primary endpoint "cosmetic outcome" will be assessed by taking the variable as response in a linear model with the randomized treatment strategy, the age of the patients and the cosmetic parameter at baseline as explanatory variables. Local control will be estimated as the parameter for randomized treatment in a Cox proportional hazard model with age as additional explanatory variable. Approved methods for censored data, such as Kaplan-Meier estimation and/or log-rank test will be applied for statistical analysis of all secondary events.

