### Study objectives

Primary objectives of the study are cosmetic result and local control rate after radiotherapy. The cosmetic result will be evaluated at 6 weeks and 2 years post radiotherapy. Local control will be evaluated at 2 and 5 years post treatment.

Secondary objectives of the trial are quality of life at 6 weeks and 2 years after radiotherapy, as well as overall survival and disease free survival at 6 weeks, 2, 5, 10 and 15 years post radiation treatment.

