### Evaluation

The cosmetic result is evaluated via photo-documentation. Before radiotherapy, 6 weeks and 2 years post treatment photographs of the patient's torso are taken in a standardized way: 2 frontal photographs from neck to midabdomen (one with arms raised and one with both arms alongside the body) and a profile photograph of the treated breast (arms raised). The pictures are evaluated by two independent investigators. Parameters to be evaluated are skin color, teleangiectasy, scars, shrinking and asymmetry. Evaluation is also carried using a quantitative digitizer scoring system, as described by Vrieling et al. [17]. Four positions are scanned on a frontal view patient photo: the mark at suprasternal notch, the mark at the midline 25 cm inferior to the suprasternal notch, the nipple position of the treated breast and the nipple position of the untreated test. These are used for the calculation of a breast retraction assessment (BRA) score. Furthermore, cosmetic evaluation is based on the standards set forth by the Harvard criteria [18]. An excellent score is given when the treated breast looks essentially the same as the contralateral, untreated breast. A good score is given for minimal but identifiable radiation effects on the treated breast, while a fair score is assigned for significant radiation effects. A poor score is used for severe sequelae of the treated breast.

Tumor manifestations within the residual breast, the regional lymphatics (axillary, parasternal, infra-/supraclavicular) or the radiation field borders are defined as locoregional relapse. Other types of tumor recurrence are considered distant metastases.

Secondary cancers must be confirmed by histological analysis. The results of the analysis should not be consistent to the original histology of the primary tumor. Date and way of diagnosis, as well as the applied dose at the site of origin of the second malignoma are documented.

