### Statistical analysis

#### Primary criteria and hypotheses

Primary aim of the study is the assessment of the cosmetic outcome and local control at 2 years after breast radiotherapy. The question to be investigated is whether intensity modulated radiotherapy (IMRT) is, in spite of the reduced treatment duration, at least equivalent to conventional therapy. The combined null hypothesis (H_0_) is "Conventional therapy is better by more than a pre-specified margin than IMRT with respect to the cosmetic outcome or local control". The alternative hypothesis (H_1_) is: "IMRT is better, or worse at most by the pre-specified margin than conventional radiotherapy with respect to both cosmetic outcome and local control". The null hypothesis will be rejected, if the lower limits of both 95 per cent confidence intervals for the effect of IMRT vs. standard are higher than the respective non-inferiority margin. The non-inferiority margins are set to a relative risk of 4.67 for local control and 1.54 for the BRA measurement of cosmesis. The non-inferiority margin for local control seems very high but it is expected to correspond to an absolute risk difference of 7 percent (from 98 to 91 per cent). The adoption of local control as a primary endpoint despite low probability of loss of local control honours the importance of the endpoint and safeguards against too severe concessions in this respect. As the total radiation dose is equivalent for both arms though, it is expected that there will be no difference in local control.

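### The 2-year cosmesis model leaves out the 6-week score, so loss before 2 years that depends on that score, unequally by arm or with an early arm difference, can bias this co-primary in either direction.

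*Protocol article*

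**What the plan says.** All places are in the protocol article, under Methods/Design.

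- Evaluation: "Before radiotherapy, 6 weeks and 2 years post treatment photographs of the patient's torso are taken in a standardized way". Study objectives agrees: "The cosmetic result will be evaluated at 6 weeks and 2 years post radiotherapy".
- Primary criteria and hypotheses sets the time point: "Primary aim of the study is the assessment of the cosmetic outcome and local control at 2 years after breast radiotherapy". Non-inferiority is judged by whether "the lower limits of both 95 per cent confidence intervals for the effect of IMRT vs. standard are higher than the respective non-inferiority margin". The cosmesis margin is "1.54 for the BRA measurement of cosmesis".
- Analysis methods gives the cosmesis model as "taking the variable as response in a linear model with the randomized treatment strategy", with "the age of the patients and the cosmetic parameter at baseline as explanatory variables". It names no 6-week term and no repeated-measures structure. It does not name the time point of the response either; 2 years is read from the hypotheses section.
- Sample size calculation plans 251 patients per arm with 10% drop-out. The drop-outs include patients "whose data files are incomplete or whose status is not properly assessed by follow-up examinations", but also patients who withdraw consent, are ineligible or are not treated to protocol.

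**The concern.** A linear model with a single 2-year response uses only patients who have that response. Someone photographed at baseline and 6 weeks but not at 2 years falls out of the comparison, although the 6-week score says something about how she would have looked at 2 years.

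This matters when return for the 2-year photograph is related to the early result. Patients know whether they had 28 or 36 fractions. Between 6 weeks and 2 years the follow-up is done by gynecologists, with no trial photograph. A link between early appearance and later attendance is therefore possible. If that link is stronger in one arm, or the arms already differ at 6 weeks, the patients left at 2 years are no longer comparable. For a non-inferiority claim, the harmful case is selective loss of IMRT patients with poor early results, which moves the estimate towards no worse. The mirror case hides non-inferiority that is there.

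**Working it through.** **Inputs from the article.** 251 per arm; 10% drop-out, so 251 × 0.9 = 225.9, or 226 evaluable; 97.5% power for cosmesis; one limit of a 95% interval compared with the margin, so one-sided 2.5%.

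**Assumed, because the article gives none of them.** Scores standardised to SD 1, higher meaning worse; correlation 0.6 between baseline and each later visit; correlation r of 0.5 or 0.7 between 6 weeks and 2 years; the whole 10% lost after the 6-week photograph, with loss logistic in the 6-week score; age left out.

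**The plan's own figure.** The 97.5% power cannot be reproduced, because no SD of the BRA score is stated. It can only be inverted: (1.96 + 1.96) × √(2/226) = 0.369 SD. If 1.54 is a difference in BRA units, the implied SD is 1.54/0.369 ≈ 4.18. With the true difference placed at the margin and no early arm difference, the error depends only on bias divided by standard error, so the missing SD does not affect those percentages.

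**Standard error of the stated model.** √(1 − 0.6²) × √(2/226) = 0.8 × 0.0941 = 0.0753 SD.

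**Bias of the stated model.** Let c be the covariance of the 6-week and 2-year scores given baseline: c = r − 0.6², so 0.34 for r = 0.7 and 0.14 for r = 0.5. In an arm losing a fraction f, with log-odds slope β per SD of the 6-week score, the mean 2-year score of those retained shifts by about −f × β × c. The bias in the arm difference is the IMRT shift minus the control shift. With f = 0.10 and odds doubled per SD (β = ln 2 = 0.693):

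| Loss depends on 6-week score in | r | Bias (SD) | Bias/SE | One-sided error |
|---|---|---|---|---|
| IMRT only | 0.7 | −0.1 × 0.693 × 0.34 = −0.0236 | −0.313 | Φ(−1.96 + 0.313) = 5.0% |
| IMRT only | 0.5 | −0.1 × 0.693 × 0.14 = −0.0097 | −0.129 | Φ(−1.96 + 0.129) = 3.4% |
| Control only | 0.7 | +0.0236 | +0.313 | Φ(−1.96 − 0.313) = 1.2% |
| Control only | 0.5 | +0.0097 | +0.129 | Φ(−1.96 − 0.129) = 1.8% |
| Both alike, no early difference | either | 0 | 0 | 2.5% |

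Simulation under the same assumptions agrees: about 5.1% and 3.4% for IMRT-only loss, 1.2% to 1.8% for control-only loss, and close to nominal when the mechanism is the same in both arms. A joint model using the 6-week score stayed near 2.5% throughout. The largest bias here is 0.0236/0.369, about 6% of the margin.

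**Early arm difference.** With one mechanism in both arms, an early difference makes the lost fractions unequal. In a harsher calculation (odds × 2.7 per SD, no baseline adjustment, r from 0.3 to 0.7), the error was 3.0% to 4.1% if IMRT was worse at 6 weeks by the margin, and 1.7% to 2.0% if it was better by that amount. In the same calculation IMRT-only dependence gave 4.8% to 9.9%. Score-dependent loss of 5% in IMRT against 15% in control gave 0.4% to 1.4%. The bias ran from −0.27 to +0.26 BRA units. Using the 6-week score brought it within 0.012 in every case.

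**Precision.** With loss unrelated to outcome, the joint model multiplies the variance by 1 − ρ² × f, where ρ = c/0.64 is the correlation given baseline. For r = 0.7, ρ = 0.53 and the factor is 0.972, about 3% more information. For r = 0.5, ρ = 0.22 and the factor is 0.995, almost nothing.

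**The case against.** The strongest reply is that a baseline-adjusted linear model is a standard analysis, and that handling of missing values belongs to an analysis plan that is not shown. The article does not say that only complete cases count. Multiple imputation from the 6-week score, followed by exactly the stated model, would deal with the same bias. This stands in part. The absence of a missing-data rule is no fault here, and the stated model is not an error. What remains is that the model as written does not use a score already collected on the same patients.

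A reader might go further and infer that loss after a poor early result will favour non-inferiority. The documents do not support that. Nothing in them indicates score-dependent loss in the IMRT arm alone, and both arms are equally aware of their treatment. The Discussion expects better cosmesis with IMRT; if that showed at 6 weeks, a common loss mechanism would work against non-inferiority. It would also be too strong to say that the stated model is valid only if loss is unrelated to the early result, since dependence that is alike in both arms, with no early difference, leaves essentially no bias.

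Two further replies stand. The 10% also covers ineligible, off-protocol and withdrawn patients, so charging all of it to loss after 6 weeks overstates the effect. And local control must pass as well, so the cosmesis errors quoted are upper bounds for a false claim by the trial as a whole.

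**Conclusion.** The point holds as a free improvement to the analysis, not as a demonstrated bias. Using the 6-week score protects the 2-year comparison against loss that depends on that score. Without it, the one-sided error at the margin is about 3% to 5% if only IMRT losses depend on the 6-week score (odds doubled per SD) and about 1% to 2% if only control losses do, against about 2.5% with it. The sign is not established. The precision gain is 0% to 3% and would not justify the change by itself.

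These sizes rest on assumed correlations (0.6 with baseline, 0.5 to 0.7 between visits), an assumed loss mechanism and loss of up to 10%. Stronger dependence or weaker baseline adjustment widens the range, as the harsher calculation shows.

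**What to change.** In Analysis methods, analyse the 6-week and 2-year cosmetic scores together in one repeated-measures linear model with arm by visit, baseline by visit, age and an unstructured covariance. Include all randomised patients with a baseline photograph and at least one follow-up photograph. Take the 2-year arm difference and its 95% confidence interval as the co-primary result; the 6-week comparison comes from the same model.

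Equivalently, keep the stated model and first multiply impute missing 2-year scores, by arm, using the 6-week score.

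Do not simply add the 6-week score as a covariate. It is measured after randomisation, so this would adjust away part of the treatment effect.

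Neither route corrects loss that depends on the unseen 2-year result; a delta-adjusted sensitivity analysis would show how far the conclusion depends on that.

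The cost is wording only. All the photographs are already planned, and no patients, visits or readers are added.

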## Methods/Design

### Trial organization

The trial has been designed by the study initiators at the Department of Radiation Oncology and the Department of Gynecology of the University of Heidelberg. The trial is carried out at the University of Heidelberg, Department of Radiation Oncology and Department of Radiation Oncology, University Medical Center Mannheim. The University of Heidelberg is responsible for trial management and coordination, as well as quality assurance including reporting, monitoring and database management.

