### Treatment planning and radiation therapy

#### Arm A

After reliable patient positioning, a thoracic CT scan with a slice distance of 3 mm is carried out. Based on the CT data set, radiation treatment planning is performed as inverse planning using the planning tool KonRad^® ^(Siemens OCS, Erlangen, Germany). Multiple fields arranged in a star-shape around the ipsilateral hemithorax are chosen. Intensity modulation is optimized according to the specified dose directions applying an inverse treatment planning technique. 6 MV-photons are used for irradiation. IMRT can be applied either in step-and-shoot technique at a linear accelerator or at a dedicated tomotherapy unit. During treatment, regular image guidance via MV-CT is carried out for positioning control.

The clinical target volume (CTV) for the residual breast tissue and - in certain cases - the locoregional lymphatics, will be defined according to the S3 guidelines of the German Cancer Society [15]. The CTV for Arm A includes the residual breast up to 5 mm under the skin surface. The primary target volume (PTV) includes the CTV with a margin of 10 mm in all directions when optimization via virtual bolus concept is possible. In Arm A/Tomotherapy or Arm A/IMRT without virtual bolus concept the PTV will not be extended over the skin surface. The GTV includes the tumor bed, as defined by preoperative mammography.

IMRT treatment is performed in 28 fractions with 1.8 Gy per fraction to a total dose of 50.4 Gy and integrated boost with 2.3 Gy per fraction to a total dose of 64.4 Gy. This is equivalent to the dose of the conventional treatment arm in consideration of the linear-quadratic model. CTV will be covered by 45 Gy, GTV will be covered by 95% of the prescribed dose i.e. 60.8 Gy. With regard to the organs at risk, less than 10% of the heart volume may receive >30 Gy, while less than 20% of the ipsilateral lung may receive more than 20 Gy. The mean dose to the contralateral breast should be limited to less than 5 Gy.

In case dose to the target volume and dose limits to the organs at risk can not be met at the same time, compliance with the threshold dose in the target volume is paramount. However, dose limitations in contralateral structures have to be met.

Treatment duration is 5^3/5 ^weeks with 5 fractions per week.

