#### Arm B

Patient positioning can be performed according to the standards of the participating medical centers and will be controlled weekly by conventional verification films. For treatment in Arm B thoracic scans with a slice distance of 10 mm are allowed.

The clinical target volume (CTV) includes the residual breast to the skin surface and in certain cases the locoregional lymphatics, according to the S3 guidelines of the German Cancer Society [15]. The primary target volume (PTV) includes the CTV with a medio-lateral and cranio-caudal margin of 10 mm, as well as a ventral margin of 20 mm. The GTV includes the tumor bed, as defined by preoperative mammography.

Conventional radiation treatment of the residual breast is performed in 28 fractions with 1.8 Gy per fraction to a total dose of 50.4 Gy. Subsequently, a consecutive boost to the tumor bed is carried out with 2 Gy per fraction in 8 fractions to a total dose of 66.4 Gy. Patients treated in Arm B receive a total of 36 fractions.

CTV will be covered by 45 Gy, GTV will be covered by 95% of the prescribed dose, i.e. 63.1 Gy. In regard to the organs at risk, less than 10% of the heart volume may receive >30 Gy, less than 40% of the ipsilateral lung may receive >20 Gy, while the mean dose in the contralateral breast should be less than 5 Gy.

In case dose to the target volume and dose limits to the organs at risk can not be met at the same time, compliance with the threshold dose in the target volume is paramount. However, dose limitations in contralateral structures have to be met.

Treatment duration is 7^1/5 ^weeks with 5 fractions per week.

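### The linear model for cosmetic outcome omits centre in a two-centre trial; adding it may give a small, unquantified gain in precision at almost no cost

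*Protocol article*

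**What the plan says.** Under Analysis methods, the protocol article specifies the cosmetic analysis as a linear model with randomised treatment, "the age of the patients and the cosmetic parameter at baseline as explanatory variables". Local control is analysed in a "Cox proportional hazard model with age as additional explanatory variable". Neither model contains centre.

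Under Trial organization there are two treating sites: "The trial is carried out at the University of Heidelberg, Department of Radiation Oncology and Department of Radiation Oncology, University Medical Center Mannheim". The Arm B section leaves one aspect of treatment to the sites: "Patient positioning can be performed according to the standards of the participating medical centers".

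Under Sample size calculation: "251 patients per trial arm are required for a power of 97.5% with reference to cosmetic result and 82.5% with reference to local control", with 10% drop-out allowed for. Under Primary criteria and hypotheses, non-inferiority is declared only if the confidence limits for both endpoints clear their margins. The article does not describe stratification of the randomisation by centre and reports no centre effect on cosmesis.

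**The concern.** The article names its covariates, so the choice can be reviewed as it stands. In a two-centre trial the treating site is known for every patient, and site is a usual candidate for adjustment. If patients at the two sites differ in cosmetic outcome after allowing for age and baseline, a model without centre leaves that difference in the residual variance. The interval for the treatment effect is then slightly wider than it needs to be. Because the decision rule compares a confidence limit with a margin, interval width bears directly on the conclusion. If the randomisation was balanced by centre, the unadjusted interval is also slightly conservative. What is at stake is precision only, and the question is how much.

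**Working it through.** **Inputs from the article.** 251 per arm, 502 in total; 10% drop-out; stated power 97.5% (cosmetic) and 82.5% (local control); 95% confidence limits, taken here as two-sided, so one-sided 0.025; local control 98%.

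**Assumption.** R² is the share of residual variance in the cosmetic model explained by centre. The article gives no figure, so a range is shown.

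**Step 1: the plan's own figure.** The 97.5% cannot be reproduced, because the article gives no SD for the BRA score. The power formula can only be inverted. Evaluable per arm: 251 × 0.9 = 225.9. The standardised margin that gives 97.5% power is (1.96 + 1.96) × √(2/225.9) = 3.92 × 0.0941 = 0.369 SD.

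**Step 2: effect of adding centre.** Evaluable in total: 502 × 0.9 ≈ 452.
- Interval-width ratio = √(1 − R²)
- Equivalent extra patients = 452 × (1/(1 − R²) − 1)
- Cosmetic power = Φ(3.92/√(1 − R²) − 1.96)
- Joint power = cosmetic power × 0.825, assuming independent endpoints
- Difference between two equal-sized centres that produces R² = 2√R², in residual SDs

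| R² | Width ratio | Patients | Cosmetic power | Joint power | Centre difference needed |
|---|---|---|---|---|---|
| 0 | 1.000 | 0 | 97.5% | 80.4% | 0 |
| 1% | 0.995 | 5 | 97.6% | 80.5% | 0.20 SD |
| 2% | 0.990 | 9 | 97.7% | 80.6% | 0.28 SD |
| 5% | 0.975 | 24 | 98.0% | 80.9% | 0.45 SD |
| 10% | 0.949 | 50 | 98.5% | 81.3% | 0.63 SD |

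**Step 3: which rows are plausible.** The 5% and 10% rows need two departments working to one protocol to differ, after baseline adjustment, by 0.45 and 0.63 SD. Both exceed the implied margin of 0.369 SD. Unequal centres reduce R² further: a 0.3 SD difference gives about 2.2% with a 50:50 split but about 1.4% with 80:20. The 2% row or below is the realistic range.

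**Step 4: cost of the term.** One degree of freedom out of about 450. If randomisation is not balanced by centre, chance correlation between centre and arm inflates the variance by about 1/451 ≈ 0.2% on average. The term therefore pays for itself once R² exceeds about 0.2%, which two equal centres reach at a difference of about 0.1 SD (R² = 0.25%).

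**Step 5: local control.** Expected events with 98% control in both arms: 0.02 × 452 ≈ 9. That is too few to justify changing the primary Cox model.

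**The case against.** The strongest reply is that nothing here is an error. Treatment, age and baseline make a valid model for a randomised comparison, and the article states no stratification by centre that the model would contradict. A condensed article may also omit covariates that the full protocol lists. The first two points stand; the last is possible, but the covariates are stated here as the model.

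Several further points limit the gain, and they also stand:
- The only practice expressly left to the centres is positioning in Arm B. Variation within one arm acts partly as a treatment-by-centre difference, which a centre main effect does not remove.
- In Arm A, "IMRT can be applied either in step-and-shoot technique at a linear accelerator or at a dedicated tomotherapy unit", but the article does not tie the platform to the centre.
- Baseline adjustment already absorbs part of any stable centre difference.
- Success needs both endpoints, and local control, with the lower stated power, limits the joint test.

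A reader might infer that photography differs between the sites and adds noise. The article does not support this: the Evaluation section describes standardised views, two independent assessors and a landmark-based BRA score. A reader might also take centre to be the known structural source of variation, but no centre effect on cosmesis is reported anywhere.

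None of these points shows a material downside to including the term.

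**Conclusion.** The point holds as a minor optional refinement. The stated cosmetic model is valid, but by leaving out centre it may give up a small amount of precision that the documents do not allow anyone to quantify. On a realistic assumption (R² of 2%, two equal centres about 0.28 SD apart), the interval would be about 1% narrower, worth about 9 of 452 patients. Cosmetic power would move from 97.5% to 97.7% and joint power from 80.4% to 80.6%. These figures rest on the assumed R², the stated powers taken at face value, one-sided 0.025 and independent endpoints.

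Two stronger readings should be resisted. One is that omitting centre biases the arm comparison. Randomisation protects against that on average, and chance imbalance in a covariate is already covered by the confidence interval. The other is that the trial forgoes the equivalent of 24 or 50 patients. Those figures need centre differences larger than the implied non-inferiority margin, and nothing in the article suggests differences of that size.

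**What to change.** Add centre as a fixed two-level term to the prespecified linear model for cosmetic outcome, next to treatment, age and baseline. This is one added term in the specification, uses one degree of freedom and needs no new data. Fixing it before the data are analysed also avoids a later choice between adjusted and unadjusted results.

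Leave the Cox model for local control unchanged. With about 9 expected events, stratification by centre belongs at most in an optional sensitivity analysis.

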### Patient selection

#### Inclusion criteria

Patients meeting the following criteria will be considered for admission to the trial:

• All patients aged >18 years and <70 years after breast conserving surgery.

• Patients aged ≥70 years with following risk factors:

○ Tumor stage ≥T2

○ Multifocal disease

○ Lymphangiosis

○ Extended intraductal component

○ Resection margin ≤3 mm

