### Study plan

502 patients (251 patients in each arm) with breast cancer and previous breast conserving surgery are included in the study according to the criteria above. Eligible patients are informed about participation in the trial with possible benefits and risks, and written informed consent is obtained. Patients are randomized into the two treatment arms after baseline photo-documentation and evaluation of the postoperative cosmetic result through an expert panel and the patient, as well as evaluation of life quality using an EORTC questionnaire.

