### Follow up

The first radio-oncologic follow-up is planned 6 weeks after treatment completion. Further trial related follow-up visits are scheduled at 2 years and 5 years post treatment. In the time between 6 weeks and 2 years, as well as between 2 and 5 years post treatment, follow-up examinations are conducted by the attending gynecologists, according to the guidelines of the German Cancer Society.

Evaluation of the cosmetic result is conducted 6 weeks and 2 years post treatment. For complete evaluation of overall survival, disease free survival, as well as possible late side-effects, e.g. secondary cancer, a follow-up period of 15 years is necessary. Therefore, further trial related documentation will be performed at 10 and 15 years post treatment.

An overview of trial related follow-up is shown in Figure 2.

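### Age is in both primary models, but only unadjusted methods are named for overall survival to 15 years; adding age is a free, minor improvement

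*Protocol article*

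**What the plan says.** Under Analysis methods, the primary cosmetic outcome goes into a linear model with "the randomized treatment strategy, the age of the patients and the cosmetic parameter at baseline as explanatory variables". Local control is analysed in a "Cox proportional hazard model with age as additional explanatory variable". For everything else that is time-to-event, the text reads: "Approved methods for censored data, such as Kaplan-Meier estimation and/or log-rank test will be applied for statistical analysis of all secondary events".

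Study objectives lists as secondary "overall survival and disease free survival at 6 weeks, 2, 5, 10 and 15 years post radiation treatment", besides quality of life. Follow up says that for these outcomes "a follow-up period of 15 years is necessary".

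Inclusion criteria admits "All patients aged >18 years and <70 years after breast conserving surgery", and then "Patients aged ≥70 years with following risk factors", with no upper age limit.

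The article states no hypothesis, margin, significance level, event count or power for overall or disease-free survival.

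**The concern.** Age is used where it may matter less and is not named where it should matter more. Local control at 2 years is expected to be about 98% in the conventional arm, and the plan adjusts that analysis for age. Over 15 years, in women from over 18 to beyond 70, age should predict death clearly, yet the methods named for that comparison ignore it.

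Leaving a strong predictor out of a survival comparison can cost power, and a chance age difference between the arms then stays in the estimated effect. The trial hopes to show survival no worse with IMRT, so precision on this endpoint is useful even though it is secondary. Age is needed for the primary models anyway.

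**Working it through.** **No plan figure to reproduce.** The article gives no power or event count for overall survival. The question is how much power age adjustment could add, and that needs assumptions.

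**Inputs from the article.** 251 patients per arm; 10% drop-out, so 251 × 0.9 = 225.9, about 226 evaluable per arm; follow-up of 15 years.

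**Assumed inputs, not in the article.** Age SD, age effect on the hazard, 15-year mortality, size of a true treatment effect and shape of the hazard.

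**Comparison.** Both analyses are tested at two-sided 5%:
- Unadjusted: log-rank test, or the equivalent Cox model with arm only.
- Adjusted: Cox model, hazard = baseline × exp(β·arm + γ·age).

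**Simulation 1.** 226 per arm, constant hazards, true treatment hazard ratio (HR) 0.6, age SD 10 years, 8000 simulated trials per row. Mortality is for the control arm. Gains are taken from unrounded powers.

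| 15-year mortality | Mean events | Age HR per SD | Unadjusted | Adjusted | Gain (points) |
|---|---|---|---|---|---|
| 15% | about 55 | 1.6 | 45.0% | 45.1% | 0.2 |
| 15% | about 55 | 2.0 | 43.5% | 45.0% | 1.4 |
| 15% | about 55 | 2.5 | 42.6% | 45.9% | 3.3 |
| 30% | about 112 | 1.6 | 73.7% | 75.5% | 1.8 |
| 30% | about 113 | 2.0 | 71.0% | 76.8% | 5.8 |
| 30% | about 114 | 2.5 | 66.2% | 76.4% | 10.3 |

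At an age HR of 1.0 to 1.3 per SD (1500 trials each) there was no gain beyond simulation error.

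**Simulation 2.** 251 per arm (no drop-out), Weibull shape 1.3, true treatment HR 1.5, age SD 11 years, 1500 trials per row. Age log-hazards of 0.04, 0.07 and 0.10 per year correspond to HRs per SD of exp(11 × 0.04) = 1.55, exp(11 × 0.07) = 2.16 and exp(11 × 0.10) = 3.00.

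| 15-year mortality | Age HR per SD | Unadjusted | Adjusted | Gain (points) |
|---|---|---|---|---|
| 20% | 1.55 | 55% | 58% | 3 |
| 20% | 2.16 | 53% | 60% | 7 |
| 20% | 3.00 | 44% | 59% | 15 |
| 35% | 1.55 | 81% | 84% | 3 |
| 35% | 2.16 | 71% | 83% | 12 |
| 35% | 3.00 | 59% | 81% | 22 |

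A separate repeat of this simulation agreed within simulation error. With 226 per arm it gave gains of 3 to 18 points.

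**Chance age imbalance.** The standard error of the difference in mean age is SD × √(2/n).
- SD 10, n = 226: 10 × √(2/226) = 0.94 years. A 1-in-20 extreme is 1.96 × 0.94 = 1.84 years, or 0.184 SD. The HR shifts by exp(0.184 × ln HR per SD): 1.05 at 1.3, 1.09 at 1.6, 1.14 at 2.0 and 1.18 at 2.5.
- SD 11, n = 251: 11 × √(2/251) = 0.98 years, extreme 1.92 years. The shift is 1.08, 1.14 and 1.21 for slopes of 0.04, 0.07 and 0.10 per year.

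**Validity.** With no treatment effect, the unadjusted log-rank test rejected in 4.0 to 5.5% of trials under the assumptions of simulation 1. A further run under those of simulation 2 gave 2.9 to 5.4%. Type I error is not inflated.

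**The case against.** The strongest reply is that the article states nothing wrong. The sentence on secondary events gives examples and joins them loosely, and a Cox model with age is also an accepted method for censored data. This is a condensed article, and covariates for secondary endpoints are commonly left to an analysis plan, which is not shown. A reader might infer that the trial is committed to an unadjusted survival comparison. The wording does not support that. What stands is narrower: the article names age for both primary models and, in the same paragraph, names only methods without it for the rest.

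A reader might also infer that the unadjusted analysis is biased, or makes a survival loss with IMRT look smaller. That does not hold either. In simulation 2 the mean unadjusted hazard ratio fell from 1.50 to between 1.48 and 1.37, but this is non-collapsibility: the marginal and age-conditional hazard ratios are different quantities. The absolute 15-year difference was recovered without bias (for example 9.3 points estimated against 9.4 true, at 35% mortality and the steepest slope). Kaplan-Meier estimates directly answer the objective, which is set at fixed time points. Chance imbalance is part of the sampling error that the test and interval already allow for, and the shifts above describe a 1-in-20 draw.

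Finally, the larger gains rest on steep assumed age effects, and adjustment cannot rescue a comparison with few deaths. At 10% mortality, power was 35% against 37% at the weakest slope and 28% against 33% at the steepest. These objections limit the point to a minor one. They do not remove it, because adjustment costs nothing and had no material downside in any setting.

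**Conclusion.** The point holds as a minor, free improvement for overall survival. The unadjusted comparison is valid but can be less powerful, and it leaves any chance age difference in the estimate.

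The power given up is about 0 to 3 points for a weak age effect (HR up to about 1.6 per SD). It is 10 points or more only for a strong age effect with substantial mortality: in these runs, 2.16 per SD at 35%, 2.5 at 30%, or 3.0 at 20%. At 15% mortality the gain was at most 3.3 points. All of this rests on an age SD of 10 to 11 years, 15-year mortality of 15 to 35%, and assumed treatment effects, none of which the article gives.

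Calling overall and disease-free survival the most age-dependent endpoints would go too far. Only mortality was simulated. The Background reports more benefit from the boost below 50 years, so age may act in opposite directions on the recurrence and death components of disease-free survival. The gain there is uncertain.

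**What to change.** In Analysis methods, state that the between-arm comparison of overall survival uses a Cox model with randomised arm and age, as already planned for local control, and that the hazard ratio is reported with its 95% confidence interval. Apply the same model to disease-free survival for consistency, without expecting a particular gain. Keep Kaplan-Meier estimates at the stated time points and the log-rank test as supporting analyses. If the analysis plan already says this, only the wording needs aligning.

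The cost is one sentence, with no new data and no extra patients. Fixing it before outcomes are compared also removes a later choice between adjusted and unadjusted results.
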